### Intervention and comparator

2.3

#### Intervention group

2.3.1

The intervention will consist of administering pectin-supplemented EN from randomization until the earliest of the following events: (1) discontinuation of gastric feeding, either due to successful transition to full oral intake or intolerance requiring a switch to post-pyloric feeding or PN; (2) ICU discharge; (3) death; or (4) 7 days after enrollment.

The pectin supplement (Yaoshun^®^ citrus pectin, Qirui medicine, China) consists of low-esterified citrus pectin with a degree of esterification of 5%–15% and is formulated to maintain relatively low viscosity during tube administration. In the presence of calcium ions contained in the enteral formula, the pectin can undergo calcium-mediated gelation, forming a semi-solid gel and increasing intragastric viscosity, which may help reduce retrograde flow and gastroesophageal reflux. The supplement will be administered at a total daily dose of 90 g per 500 mL of enteral formula, delivered as divided 45 g boluses via gastric tube. One bolus will be administered immediately before initiation of EN, with subsequent boluses given after every 250 mL of formula infusion. To minimize the risk of tube occlusion, the feeding tube will be flushed with 20 mL of warm water before and after each pectin administration.

#### Control group

2.3.2

The comparator will be usual nutritional care, delivered and managed in accordance with the CCCNTG feeding protocol^2^ based on international guidelines (19).

#### ICU procedures common to both arms

2.3.3

Once randomized, the treating clinical team will determine the target infusion rate (mL/hour) for continuous EN to meet the energy requirement. Selection of the EN formula, estimation of protein needs, and blood glucose management will follow the CCCNTG feeding protocol or the standard procedures of each participating site.

Feeding intolerance will be managed according to the CCCNTG feeding protocol. Initial strategies include the use of prokinetic agents (e.g., erythromycin, metoclopramide) and adjustments to the EN formula. For patients with persistent gastric intolerance despite prokinetic therapy, postpyloric feeding will be implemented. If intolerance continues even after postpyloric feeding is attempted, PN will be commenced.

All patients will receive routine clinical care as determined by the local ICU team, including monitoring of vital signs, analgesia and sedation, fluid therapy, mechanical ventilation, renal replacement therapy, and vasoactive support. All cointerventions will be undertaken at the discretion of the treating clinicians and documented in the medical record.

### Study outcomes and their measures

2.4

#### Primary outcome

2.4.1

The primary outcome of this study is the ratio of EN energy intake to the prescribed target energy on Day 5 after randomization. Patients who died before Day 5 will not be included in the analysis of the primary outcome. Patients who were discharged from ICU before Day5 will be followed up after ICU discharge.

Target energy requirements will be estimated using a simple weight-based equation of 25 kcal/kg of body weight. Body weight used for calculating energy requirements will follow the recommendations of the 2023 ESPEN guideline (2): actual body weight will be used if the body mass index (BMI) is ≤25. For patients with BMI > 25, an adjusted body weight will be applied, defined as:

Adjusted body weight = Ideal body weight + 25% × (actual body weight–ideal body weight). Ideal body weight (kg) will be determined using the formula: 0.9 × height (cm)–100 for males, and 0.9 × height (cm)–106 for females.

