#### Inclusion criteria

2.1.1

1. Aged ≥ 18 years old;

2. Admitted to ICU < 24 h;

3. Receive invasive mechanical ventilation < 72 h, and the expected duration of continued treatment > 48 h;

4. Do not expect to feed orally for more than 3 days and plan to receive gastric feeding;

5. No operation plan within a week;

6. Informed consent form obtained from the patient or next of kin.

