#### Secondary outcomes

2.4.2

Part I: Clinical outcomes

1. Duration of ICU stay.

2. Duration of mechanical ventilation.

3. Duration of hospital stay.

4. 28-day mortality.

5. ICU-free to 28 days.

6. Hospital-free days to 28 days.

7. Ventilation-free days to 28 days.

8. Incidence of new-onset organ failure within 7 days after enrollment.

9. New receipt of organ support within the first 7 days.

10. Number of organ support–free days within the first 7 days.

11. Daily Sequential Organ Failure Assessment (SOFA) scores recorded over the first 7 days.

Part II: Nutritional outcomes

1. Time to initiation of EN.

2. Average daily energy intake within the first 7 days.

3. Average daily protein intake within the first 7 days.

4. Daily Bristol stool score within the first 7 days.

5. Daily Feeding Intolerance Score (FIS) (20) within the first 7 days (Supplementary Table 1).

6. Daily Gastrointestinal Dysfunction Score (GIDS) (21) within the first 7 days (Supplementary Table 2).

7. Proportion of patients who transition to postpyloric feeding within the first 7 days.

8. Proportion of receiving PN within the first 7 days.

9. Caloric adequacy on Days 3, 5, and 7, defined as achieving at least 80% of the estimated energy target.

10. Protein adequacy on Days 3, 5, and 7, defined as achieving at least 70% of a target of 1.3 g/kg/day.

Part III: Biochemical outcomes

Daily serum albumin, prealbumin, C-reactive protein (CRP), and blood urea nitrogen (BUN) during the first 7 days after enrollment.

Outcome definitions are as follows. *New-onset organ failure* is defined as failure arising in an organ system that was functionally intact at randomization, corresponding to an increase of ≥2 points in the SOFA sub-score for the respiratory, circulatory, or renal system relative to baseline. SOFA scores are assessed daily for the first 7 days following randomization. *New receipt of organ support therapy* refers to the initiation of mechanical ventilation, renal replacement therapy, or vasoactive agents that were not being used at enrollment. *Daily energy and protein intake* will be calculated based on EN, PN, and quantifiable oral nutritional supplements, with non-quantifiable oral intake excluded.

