### Data analysis

2.7

Reporting and presentation of trial results will adhere to the Consolidated Standards of Reporting Trials (CONSORT) guidelines (22). The primary analysis will be conducted according to the intention-to-treat (ITT) principle, with secondary supportive analyses performed in the per-protocol (PP) population and safety analyses in the safety population.

Analysis populations are defined as follows. The ITT population comprises all randomized participants. The PP population comprises participants who completed the intervention in accordance with the study protocol, excluding those with major protocol deviations, defined as: (a) enrollment of participants subsequently confirmed ineligible; (b) receipt of <80% of the planned pectin dose. All deviations will be prospectively recorded in a Protocol Deviation Log in the eCRF and reviewed by the TMC at each monitoring visit. The safety population comprises all participants who received at least one dose of the study intervention.

Primary outcome analysis: Patients who die before Day 5 are excluded from the primary analysis as a pre-specified competing event. A sensitivity analysis will assign these patients an EN delivery ratio of 0% (worst-case assumption), reported alongside the primary complete-case analysis. Administratively missing primary outcome data are anticipated to be <5% based on prior NEED trial experience (19) and will be handled by complete-case analysis with transparent reporting of the missing data rate. The number of deaths before Day 5 in each arm will be reported in the CONSORT flow diagram and primary analysis table to ensure full ITT accounting.

Time-to-event analyses: A competing risks framework using the Fine-Gray subdistribution hazard model, with death as the competing event, will be applied to time-to-event outcomes including time to achieve ≥ 80% of the prescribed EN target, time to ICU discharge, and time to hospital discharge, etc. Kaplan-Meier curves for 28-day mortality will be presented for both groups with log-rank comparison.

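### The Day-5 ratio counts EN energy only and has a scoring rule only for death, so a patient who has recovered to full oral feeding takes the value 0%

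*Protocol article*

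**What the plan says.** Section 2.4.1 of the Protocol article defines the endpoint: "The primary outcome of this study is the ratio of EN energy intake to the prescribed target energy on Day 5 after randomization". It then deals with two events. For death: "Patients who died before Day 5 will not be included in the analysis of the primary outcome". For early ICU discharge: "Patients who were discharged from ICU before Day5 will be followed up after ICU discharge". Section 2.7 adds a sensitivity analysis that sets deaths before Day 5 to 0%, and states: "The ITT population comprises all randomized participants".

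Section 2.3.1 lists what ends the intervention within the 7-day window. One item is "discontinuation of gastric feeding, either due to successful transition to full oral intake or intolerance requiring a switch to post-pyloric feeding or PN". Section 2.3.3 applies the same rescue pathway to both arms: "For patients with persistent gastric intolerance despite prokinetic therapy, postpyloric feeding will be implemented".

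For the secondary outcomes of daily energy and protein intake, section 2.4.2 uses a wider numerator. They "will be calculated based on EN, PN, and quantifiable oral nutritional supplements, with non-quantifiable oral intake excluded". That rule is not applied to the primary ratio.

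**The concern.** The protocol foresees two opposite reasons for gastric feeding to stop. One patient has recovered and eats. Another has not tolerated gastric feeding and is moved to a post-pyloric tube or PN. The primary ratio has no rule for either, so its definition decides the score.

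- **Full oral intake, no EN on Day 5.** The numerator is zero, so the ratio is 0%. A good course gets the same number that the sensitivity analysis reserves for death.
- **Post-pyloric rescue.** Post-pyloric feeding is still EN and nothing restricts the numerator to gastric delivery, so whatever is delivered is credited in full. The ratio cannot separate a patient who tolerated gastric feeding from one who failed it and was rescued effectively.

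What is at stake is interpretation. If one arm has more early recovery, or the other more successful rescue, a null or reversed difference could arise for reasons unrelated to poor delivery. The planned analyses in the article would not show that this had happened.

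**Working it through.** **1. The plan's own figure.** Inputs from section 2.6: control mean 62.9%, SD 31.1%, relative increase 20%, power 80%, two-sided alpha 0.05, allocation 1:1.

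- Target difference: 0.20 × 62.9 = 12.58 points, that is 75.48% against 62.9%.
- Per arm: n = 2 × (1.960 + 0.842)² × 31.1² / 12.58² ≈ 96, as stated.
- With 10% added: 96 × 1.1 = 105.6, so 106 per arm and 212 in total, as stated.

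The sample-size arithmetic is not in dispute.

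**2. Can the event occur by Day 5?** The inclusion criteria (section 2.1.1) require: "Do not expect to feed orally for more than 3 days and plan to receive gastric feeding". They also require more than 48 hours of expected further ventilation. Neither excludes oral feeding by Day 5. Section 2.4.1 also provides for ICU discharge before Day 5, although discharge does not by itself mean eating.

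**3. Score of a fully oral patient.** Ratio = EN energy / target = 0 / target = 0%. This is implied by the definition, not written. It holds only when no EN is given that day; a patient still receiving some EN scores above 0%.

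**4. Effect of unequal oral transition.** Let q be the share scoring 0% in an arm and m the mean ratio among the rest. The arm mean is (1 − q) × m, so a difference in q of 0.05 shifts the contrast by 0.05 × m.

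- With m = 62.9 and no true effect: 0.05 × 62.9 = 3.1 points, and 3.1 / 12.58 = 25% of the target difference.
- With m = 75.48 in the arm with more recovery: 0.05 × 75.48 = 3.8 points.

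The shift goes against the arm with more recovery. The article gives no oral rate, so the 5-point gap is an assumption.

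**5. Post-pyloric credit.** Let f be the share with gastric failure, m the mean ratio without failure and r the mean ratio in rescued patients. The between-arm difference is (f control − f pectin) × (m − r). Assume f = 30% against 20% and m = 75%:

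| Mean ratio in rescued patients, r | Difference in points |
|---|---|
| 0% (failure earns nothing) | 0.10 × 75 = 7.5 |
| 40% | 0.10 × 35 = 3.5 |
| 62.9% | 0.10 × 12.1 = 1.2 |
| 80% | 0.10 × (−5) = −0.5 |

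The better the rescue works, the less of a true difference in gastric failure the ratio shows. The failure shares, m and r are all assumed, so the table shows the mechanism and is not a forecast.

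**The case against.** Four objections have weight.

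**Power.** A reader might infer that the zeros erode the planned power. Adding equal shares of 5%, 10% or 20% zeros to the planning distribution raises the SD to 33.9, 36.1 or 39.3 and lowers power at 96 per arm to 69%, 58% or 43%. The article does not support that reading. Section 2.6 takes 62.9% (31.1%) from the same EN-only Day-5 ratio in ventilated patients and states no exclusion of oral or rescued patients. Those figures may already contain the zeros, and adding more would then count them twice. This objection stands.

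**Rescue scored as success.** A reader might also infer that a rescued patient is scored as a success. The outcome is continuous with no threshold, so that patient is credited only with the energy delivered. The Introduction itself describes the stepwise rescue as slow and not always effective, so some Day-5 penalty is plausible. This stands.

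**Aim.** The Abstract gives the aim as EN delivery. Counting EN by any tube is a coherent choice for that aim. Gastric tolerance is covered by secondary outcomes: daily FIS and GIDS, post-pyloric transition and PN use. This stands for the post-pyloric half of the point. It does not explain why a recovered patient should score 0%.

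**Direction and scope.** Nothing in the article shows that pectin speeds oral feeding, so the direction of any imbalance is unknown. Handling of such events is also often left to an analysis plan. Here, however, the article fixes the numerator and writes rules for death and discharge. The 0% follows from what is stated, so it is more than an omitted detail.

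**Conclusion.** The point holds in a limited form. Applied as written, the primary outcome gives 0% to a patient on full oral intake with no EN on Day 5, and it does not distinguish gastric tolerance from successful post-pyloric rescue. The first is a perverse score. The second is a defensible choice that needs a supporting analysis to be interpretable.

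On the mean-difference scale used for the sample size, each 5-point gap in oral transition moves the estimate by about 3.1 points. This rests on a mean of 62.9% among patients still on EN and on an imbalance that the article neither reports nor rules out. No loss from the stated 80% power is demonstrated, and no bias against pectin in particular is shown.

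**What to change.** Keep the Day-5 ratio as the primary outcome. Before unblinding:

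1. State in one sentence how full oral intake on Day 5 is scored in the primary analysis.
2. Pre-specify a sensitivity analysis in which these patients do not score 0%. For example, exclude them as a recovery event, or use the ratio on their last full day of tube feeding.
3. Add a supportive analysis with post-pyloric energy set to zero, where the route is recorded.
4. Report by arm the numbers on oral intake, on post-pyloric feeding, on PN, discharged and dead at Day 5. Deaths before Day 5 by arm, and post-pyloric and PN use over 7 days, are already planned.

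The cost is wording and some extra analysis. Table 2 schedules daily energy intake on Days 1 to 7, and the planned time to 80% of the EN target implies that EN energy is followed over time. The article does not show whether EN energy is recorded by tube position, so item 3 depends on that. Both alternatives in item 2 have a weakness: exclusion conditions on a post-randomization event, and an earlier day's value may come from a period when feeding was still being built up or weaned. They therefore fit a sensitivity analysis better than a replacement for the primary one.

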### Sample size estimation

2.6

Based on a previous nationwide multicenter trial (the NEED trial) conducted by the CCCNTG (19), among patients receiving invasive mechanical ventilation, the mean (standard deviation) ratio of EN energy intake to the prescribed target energy on Day 5 was 62.9% (31.1%) in the control group. Assuming a minimal clinically meaningful relative increase of 20% in the intervention group, with 80% power, a two-sided alpha of 0.05, and a 1:1 allocation ratio, the required sample size is 96 participants per arm (PASS ver.11.0; NCSS, LLC). To account for potential attrition, including withdrawal or dropped, estimated at approximately 10%, the final sample size was increased to 212 participants (106 per group).

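### The ideal body weight formula, as printed, gives implausible weights (clearest in women) and feeds the primary-outcome denominator for every patient with BMI above 25

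*Protocol article*

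**What the plan says.** All of this is in the protocol article, section 2.4.1 (Primary outcome), unless another section is named.

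- Endpoint: "The primary outcome of this study is the ratio of EN energy intake to the prescribed target energy on Day 5 after randomization".
- Denominator: "Target energy requirements will be estimated using a simple weight-based equation of 25 kcal/kg of body weight".
- Weight to use: "actual body weight will be used if the body mass index (BMI) is ≤25". Above BMI 25 the plan switches to a corrected weight, given by this equation: "Adjusted body weight = Ideal body weight + 25% × (actual body weight–ideal body weight", with the closing bracket following.
- Ideal weight: "0.9 × height (cm)–100 for males, and 0.9 × height (cm)–106 for females". No brackets enclose the subtraction.

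The choice of weight is attributed to a cited 2023 guideline. The article gives no worked example and no second definition of ideal weight.

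The target is also used elsewhere. Section 2.4.2 defines caloric adequacy on Days 3, 5 and 7 as reaching at least 80% of it. Section 2.3.3 has the treating team set the infusion rate to meet the energy requirement. Section 2.7 lists a BMI subgroup split at 25, the same point at which the weight rule changes.

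**The concern.** Multiplication comes before subtraction, so the printed text means 0.9 times height, minus 100 or 106. For women of ordinary height the result is too low to be called ideal. Loss of a bracket in converting the page to text is unlikely, because the brackets in the adjusted-weight equation just above, and around the unit of height, are present.

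The formula helps to define the primary endpoint. If it is not the intended one, the ratio for every patient with BMI above 25 is measured against an unintended target, and some of those patients change sides of the 80% adequacy cut-off. If sites, the eCRF and the analysis programs read the line differently, the denominator is not uniform across the trial. Section 2.1 says recruitment began in February 2024, so patients may already have been handled under one reading or another.

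**Working it through.** **Inputs.** From section 2.4.1: 25 kcal/kg, the BMI 25 switch, the 25% adjustment and the two ideal-weight formulas. Heights are not in the document. I assume 150 and 160 cm for women and 170 cm for men as examples.

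**The plan's own figures.** The article prints no ideal-weight value to reproduce. Its sample size does reproduce: a 20% relative increase on 62.9% is 12.58 points. With SD 31.1, 80% power and two-sided alpha 0.05, this needs 96 per arm. That calculation does not use the weight formula.

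**Step 1: ideal weight as printed.**
- Woman 150 cm: 0.9 × 150 − 106 = 29.0 kg; BMI 29.0 / 1.50² = 12.9
- Woman 160 cm: 0.9 × 160 − 106 = 38.0 kg; BMI 38.0 / 1.60² = 14.8
- Man 170 cm: 0.9 × 170 − 100 = 53.0 kg; BMI 53.0 / 1.70² = 18.3

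**Step 2: comparison reading, for scale only.** With the subtraction bracketed, 0.9 × (height − 106 or − 100):
- Woman 160 cm: 0.9 × 54 = 48.6 kg (BMI 19.0)
- Man 170 cm: 0.9 × 70 = 63.0 kg (BMI 21.8)

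**Step 3: weight of the formula in the target.** Adjusted weight = ideal + 0.25 × (actual − ideal) = 0.75 × ideal + 0.25 × actual. The two readings of ideal weight differ by 10.6 kg in women and 10 kg in men at any height. The targets therefore differ by 25 × 0.75 × 10.6 = 199 kcal/day (women) and 25 × 0.75 × 10 = 187.5 kcal/day (men) for everyone with BMI above 25, and by nothing at or below it.

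**Step 4: the step at BMI 25.**

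| | Target at BMI 25 (actual weight) | Just above, as printed | Just above, bracketed |
|---|---|---|---|
| Woman 160 cm, 64 kg | 25 × 64 = 1,600 kcal | 25 × (28.5 + 16) = 1,113 (−30%) | 25 × (36.45 + 16) = 1,311 (−18%) |
| Man 170 cm, 72.25 kg | 25 × 72.25 = 1,806 kcal | 25 × (39.75 + 18.06) = 1,445 (−20%) | 25 × (47.25 + 18.06) = 1,633 (−10%) |

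Just above the switch, the printed rule gives this woman the target of a woman of her height weighing 44.5 kg.

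**Step 5: the ratio at BMI 28, intake held fixed.**
- Woman 160 cm, 71.7 kg: 1,160 kcal printed against 1,359 bracketed. The ratio is 1,359 / 1,160 = 1.17 times as high, about 17% in relative terms.
- Man 170 cm, 80.9 kg: 1,500 against 1,687. The ratio is 1.125 times as high, or 12.5%.

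**Step 6: the adequacy cut-off.** An intake of 930 kcal in that woman is 930 / 1,160 = 80% as printed, which meets the cut-off, and 930 / 1,359 = 68% bracketed, which does not.

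**The case against.** Most of the case on the other side concerns the size of the harm, and much of it stands.

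- **Bias.** A reader might infer that the formula biases the treatment comparison. The document does not support this. The rule depends on height, weight and sex and is the same in both arms.
- **The 20% effect.** It is tempting to set the 12.5% to 17% shift beside the 20% relative increase in section 2.6 and call them similar in size. They are different quantities: one is a change in the level of the ratio within a BMI group in both arms, the other a difference between arms.
- **Fixed intake.** The shift assumes that delivery does not respond to the target. Section 2.3.3 sets the infusion rate to meet the requirement, so numerator and denominator may move together, and the shift would then be smaller.
- **Noise.** Any loss of power is small. Suppose 20% to 50% of patients have BMI above 25 (not in the document), their ratios rise by 12% to 19% in both arms, intake is fixed, and the section 2.6 mean and SD hold otherwise. The standardised effect then falls from 0.404 to between 0.397 and 0.402. Power at 96 per arm falls from 79.6% (by the t distribution) to about 78% to 79%.
- **The step at BMI 25.** About 10 of the 20 points in the man and 18 of the 30 in the woman remain under the bracketed reading, because the plan switches from actual to adjusted weight there.
- **Men.** The result for men is borderline, and the document gives no threshold against which to call it underweight.
- **Source.** The guideline is not at hand. The line may be a misprint or may match its source, and the article cannot show what the eCRF computes. Nor does it say which formula lay behind the 62.9% planning value, so a mismatch there is only a possibility.

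None of this makes 38 kg at 160 cm, or 29 kg at 150 cm, a credible ideal weight.

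**Conclusion.** The point holds as a defect in the definition of the primary-outcome denominator. As printed, the formula gives implausible ideal weights, clearly so in women. It enters the target of every patient with BMI above 25 with a weight of 75%. Against the bracketed reading, the target is lower by 199 kcal/day in women and 187.5 kcal/day in men. For a fixed intake at BMI 28, the ratio is higher by about 17% (160 cm woman) or 12.5% (170 cm man) in relative terms, and by less if delivery follows the target.

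What is affected is the level and validity of the ratio, classification at the 80% cut-off, and the BMI subgroup, whose boundary coincides with the change of rule. The randomised comparison is not biased by this alone, and the sample size is untouched. The shift in the overall mean cannot be computed, because the share of patients with BMI above 25 is not given.

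A reader might also conclude that the bracketed formula is the right one. The document does not establish that. It serves here only as a yardstick, and I take no view on which energy target is correct. The figures rest on the assumed heights and on reading the line by ordinary operator order.

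**What to change.** 1. Verify the printed ideal-weight formula against the guideline that section 2.4.1 cites for the weight rule, and state it unambiguously, with brackets where they are meant and one worked value for each sex.
2. Reconcile the protocol text with the calculation in the eCRF and with any feeding-target tool used at the sites.
3. Check and document which version was applied to patients already enrolled.
4. For the analysis, compute the denominator centrally for all patients from recorded height, weight and sex, using the one verified formula, and derive 80% caloric adequacy from the same value.

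The cost is low: a one-line correction or confirmation, a check of the eCRF and of past use, and a programmed recalculation from height, weight and sex. No change to the sample size is needed. Which target is clinically right is for the sponsor to settle from its source.
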